## Abstract

**Introduction:**

Increasing evidence suggests obesity has its origins prior to birth. There is clear correlation between maternal obesity, high birthweight and offspring risk of obesity in later life. It is also clear that women who are obese during pregnancy are at greater risk of adverse outcomes, including gestational diabetes and stillbirth. The mechanism(s) by which obesity causes these problems is unknown, although hyperglycaemia and insulin resistance are strongly implicated. We present a protocol for a study to test the hypothesis that metformin will improve insulin sensitivity in obese pregnant women, thereby reducing the incidence of high birthweight babies and other pregnancy complications.

**Methods and analysis:**

The Efficacy of Metformin in Pregnant Obese Women, a Randomised controlled (EMPOWaR) trial is a double-masked randomised placebo-controlled trial to determine whether metformin given to obese (body mass index >30 kg/m^2^) pregnant women from 16 weeks’ gestation until delivery reduces the incidence of high birthweight babies. A secondary aim is to test the mechanism(s) of any effect. Obese women with a singleton pregnancy and normal glucose tolerance will be recruited prior to 16 weeks’ gestation and prescribed study medication, metformin or placebo, to be taken until delivery. Further study visits will occur at 28 and 36 weeks’ gestation for glucose tolerance testing and to record anthropometric measurements. Birth weight and other measurements will be recorded at time of delivery. Anthropometry of mother and baby will be performed at 3 months postdelivery. As of January 2014, 449 women had been randomised across the UK.

**Ethics and dissemination:**

The study will be conducted in accordance with the principles of Good Clinical Practice. A favourable ethical opinion was obtained from Scotland A Research Ethics Committee, reference number 10/MRE00/12. Results will be disseminated at conferences and published in peer-reviewed journals.

**Trial registration number:**

ISRCTN51279843.

Strengths and limitations of this studyThis is the first multicenter, double-masked, randomised controlled trial to examine the effect of metformin in obese pregnant women without diabetes.We will use a recognised surrogate (birthweight centile) as a marker of future life risk of obesity in the offspring.Follow-up of the offspring is limited to the early postnatal phase.

## Background, including rationale and any previous systematic reviews

Rates of obesity, as defined by a body mass index (BMI) greater than 30 kg/m^2^, are rising alarmingly in the UK and throughout the world. Around 27% of adults in Scotland are now obese and 32% of Scottish children have a weight outwith a healthy range for their age.^1^ Obesity rates in England^2^ and the USA^3^ are similar. The increase in average BMI during pregnancy over the past 20 years has been well documented.^4^ Rates of maternal obesity in women booking for antenatal care in the UK are now around 20%. There has also been a substantial increase in mean birth weight and in the incidence of being born large for gestational age over the past few decades.^5^ The secular rise in maternal weight at delivery appears to be the factor most strongly correlated with the increase in birth weight.^5^
^6^ Positive correlations have also been shown between birth weight and both maternal pregravid weight^7–9^ and weight gain in pregnancy,^10^ with odds of high birth weight some 2.4 times greater in morbidly obese compared with lean women.^11^

This increase in mean birth weight is of concern because it is linked to an increased likelihood of child and adult obesity. A systematic review showed a positive correlation between birth weight and obesity during adulthood.^12^ The association between high birth weight and later life obesity is also supported by two large epidemiological studies^13^
^14^ both of which found obesity to be a long-term correlate of high birth weight. A subsequent prospective study found that children who were large for gestational age at birth and exposed to an intrauterine environment of maternal obesity are also at increased risk of developing metabolic syndrome.^15^ Our own recent work suggests that offspring of obese pregnant women are at increased risk of premature death in adulthood.^16^ Thus, the increase in rates of maternal obesity are setting up a vicious cycle, leading to increased birth weight and increased rates of child and adult obesity, contributing to an epidemic of obesity which has become one of the most significant contributors to global ill health.

Women who are obese during pregnancy are also themselves at greater risk of a number of adverse outcomes, including gestational diabetes,^17^ pre-eclampsia^18^ and stillbirth.^19^
^20^ The mechanism(s) by which maternal obesity increases pregnancy and peripartum complications are unclear, but there are likely several candidate mechanisms including hyperglycaemia and increased insulin resistance.

Clearly an intervention is urgently required. Lifestyle interventions (eg, diet and exercise) are a logical approach and are currently being trialled, for example, UK Pregnancies Better Eating and Activity Trial (UPBEAT), Poston (ISRCTN89971375) although studies hitherto have shown no evidence of benefit.^21–23^ A recent meta-analysis of dietary and lifestyle interventions suggests dietary interventions may be of some benefit over physical activity or mixed interventions in reducing maternal weight gain. However, there was no effect on birth weight, the incidence of large for gestational age babies and clinically important adverse outcomes.^24^

In this study, we test the hypothesis that the insulin-sensitising agent metformin reduces birthweight centile in the offspring of obese pregnant women. The principal action of metformin includes improvement of insulin resistance in the liver and skeletal muscle, along with improved endothelial function, increased peripheral uptake of glucose, improved lipid profile, redistribution of fat from visceral to subcutaneous depots and antioxidant effects,^25^ all of which are likely to contribute to its clinical efficacy in reducing adverse outcomes in obese pregnant women.

Considerable evidence implicates insulin resistance or hyperglycaemia as the mechanism by which maternal obesity causes excessive neonatal birth weight. While modest insulin resistance is physiological in pregnancy and generates maternal glucose, free fatty acids and amino acids as substrates for fetal growth, obese pregnant women are more insulin resistant than their lean counterparts^6^ leading to a further amplification of nutrient availability with consequent excessive fetal growth. There is a strong correlation between insulin resistance in late gestation and both birth weight and fat-free mass at birth.^26^ The Hyperglycaemia and Adverse Pregnancy Outcomes (HAPO) trial^27^ confirms that there is a linear relationship between hyperglycaemia and birth weight, even at glucose levels not usually considered abnormal during pregnancy. The Australian Carbohydrate Intolerance Study in Pregnant Women (ACHOIS)^28^ confirms that treating hyperglycaemia can substantially reduce both the incidence of large for gestational age babies and other perinatal complications. Thus, metformin, by reducing insulin resistance, could have a major impact in reducing excess birth weight in obese pregnant women.

This study is timely because of emerging evidence about the safety and efficacy of metformin. It is a licensed first-line therapy for the treatment of type 2 diabetes and is endorsed by National Institute for Health and Care Excellence (NICE) as a treatment for gestational diabetes.^29^

There are few previous studies testing the effects of metformin in pregnant women in the absence of diabetes. A small randomised study of 40 pregnant women with a history of polycystic ovarian syndrome (PCOS), a condition often accompanied by insulin resistance, showed that metformin reduced predefined pregnancy complications from 32% in the placebo group (n=22) to 0% in the metformin group (n=18; p=0.01).^30^ However, a larger study by the same group, which randomised 274 women with PCOS to either metformin or placebo throughout pregnancy, showed no significant differences in the prevalence of preterm birth, pre-eclampsia and gestational diabetes.^31^ There was also no difference in birth weights of the babies in the two groups. However, the mean BMI of the participants in these studies was less than 30 kg/m^2^. In the Metformin in Gestational diabetes (MiG) study, which compared the effect of metformin versus insulin in women with gestational diabetes,^32^ there were no differences in birth weight between the offspring. However, weight gain in pregnancy, a known additional driver of birth weight,^7^ was lower in the metformin group (difference of 1.6 kg, p<0.001). By 2 years of age, offspring of the participants randomised to metformin had greater subcutaneous fat, but overall body fat was the same as in children whose mothers were treated with insulin alone, suggesting that the ‘metformin offspring’ have smaller deposits of visceral, metabolically active fat.^33^ Further follow-up is required to examine whether these findings persist into later life and whether children exposed to metformin will be more insulin sensitive.

Importantly, if metformin is to be effective in reducing high birth weight in obese women, it should not increase the proportion of babies with low birth weight. The studies aforementioned, and another small study, on women with a mean BMI less than 30 kg/m^2^ are reassuring on this point.^30^
^31^
^34^

## Hypothesis

We hypothesise that metformin administered to obese women during pregnancy will reduce birthweight centile in their babies and consequently their future life risk of obesity and metabolic syndrome.

## Aim

To determine if metformin administered to obese women during pregnancy reduces birthweight centile in their babies, using birth weight as a surrogate marker of the future life risk of obesity and metabolic syndrome in the offspring.

## Objectives

### Primary objective

To determine the efficacy of metformin (up to 2500 mg daily), given to obese pregnant women from between 12 and 16 weeks’ gestation until delivery, in reducing gestational age-adjusted and sex-adjusted birthweight centile of the baby.

### Secondary objectives

To determine the pattern of association between insulin resistance and adverse pregnancy outcomes, including incidence of pregnancy-induced hypertension, pre-eclampsia, caesarean section, postpartum haemorrhage, maternal weight gain during pregnancy and incidence of the baby's admission to the neonatal unit.To determine the effect of metformin on maternal body composition.To determine the effect of metformin on neonatal body composition.To determine the effect of metformin on maternal inflammatory and metabolic variables (measured at 28 and 36 weeks’ gestation) and on neonatal inflammatory variables (measured in cord blood at birth).To confirm that metformin does not increase the rate of babies with a low birthweight centile.To determine the efficacy (as opposed to the effectiveness) of metformin when analysis is restricted to those with pharmacological circulating levels of drug.A series of nested substudies will also be performed with the following objectives:
To determine the effect of metformin on maternal cortisol levels in obese pregnant women.To determine the effect of metformin in hepatic and peripheral insulin sensitivity at 36 weeks’ gestation in obese pregnant women.To determine the effect of metformin on endothelium-dependent flow-mediated dilatation in obese pregnant women.To determine the effect of metformin on maternal subcutaneous and visceral adipose tissue deposition and hepatic and skeletal muscle ectopic fat deposition during pregnancy.To determine the effect of metformin on fetal liver volume and subcutaneous fat deposition.To determine the effect of metformin on myometrial contractility and myometrial glycogen storage in obese pregnant women.To determine the effect of metformin on placental glucocorticoid receptor and 11 βHSD 1 and 2 mRNA levels.

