## Randomisation

Eligible participants will be randomly assigned to active treatment with metformin or an identical looking placebo. This will be documented in the patient's paper case record and/or computer file to show the woman's participation in the trial.

Participants will be randomised via a web portal connected to a central randomisation facility based at the trial data centre, the Edinburgh Clinical Trials Unit, University of Edinburgh. Baseline eligibility data will be required before randomisation. Participants will be randomised in a 1:1 ratio to metformin or placebo. Randomisation will be stratified by treatment centre and BMI 30–39 vs >40 kg/m^2^.

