### Dose changes

The local investigator or participant may alter the treatment regimen at his/her discretion, so long as the maximum daily dose does not exceed 2500 mg. Changes to the treatment dose will be recorded in the electronic case report form (eCRF) as soon as practicable.

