## Participant compliance

Compliance will be recorded in a treatment diary and by counting of unused tablets. Additionally, gas chromatography mass spectrometry will be used to analyse metformin levels in blood samples from participants in the third trimester.

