### Secondary outcomes

Maternal insulin resistance at 36 weeks’ gestation, which will be correlated with adverse pregnancy outcomes.Maternal anthropometry and body composition at 16 and 36 weeks’ gestation and 3 months postpartum.Baby anthropometry and body composition at birth and 3 months of age.Maternal inflammatory markers, lipid and fatty acid indices prior to starting treatment and again at 28 and 36 weeks’ gestation including CRP, IL-6, leptin, lipid profile, non-esterified fatty acids, polyunsaturated fatty acids and PAI1/PAI2 ratio.Neonatal CRP, glucose, insulin and other inflammatory and metabolic indices as previously described (measured in cord blood at birth).Incidence of low birthweight centile.Gas chromatography mass spectrometry measurement of metformin in maternal plasma to determine adherence.Secondary outcomes from nested substudies;
Maternal salivary cortisol levels at baseline, 28 and 36 weeks’ gestation.Hepatic and peripheral insulin sensitivity at 36 weeks’ gestation as measured by the hyperinsulinaemic euglycaemic clamp technique.Maternal brachial artery endothelium flow-mediated dilatation measured at 16 and 36 weeks’ gestation.Maternal subcutaneous and visceral adipose tissue deposition and hepatic and skeletal muscle ectopic fat deposition assessed using MRI and magnetic resonance spectroscopy.Fetal liver volume and fetal subcutaneous fat deposition assessed using MRI.In vivo measurements of myometrial contractility on myometrial biopsies obtained at the time of caesarean section.Placental glucocorticoid receptor and 11 βHSD 1 (β hydroxysteroid dehydrogenase 1) and 2 mRNA levels.

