### Type of analysis and statistical tests

The primary analysis will be by intention to treat. Mean birthweight centile will be compared between the two groups using a two-sample t test, but with the analysis stratified for the same factors as the randomisation. Correlations within the metformin and placebo groups will be used to determine associations between insulin resistance and adverse pregnancy outcomes.

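### The secondary efficacy objective selects women on a third-trimester metformin level, which essentially only the metformin arm can have, so it is not a randomised comparison and is open to selection bias

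*Protocol article*

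**What the plan says.** Under Secondary objectives the protocol article sets this aim: "To determine the efficacy (as opposed to the effectiveness) of metformin when analysis is restricted to those with pharmacological circulating levels of drug". Participant compliance says how and when the level is obtained: "gas chromatography mass spectrometry will be used to analyse metformin levels in blood samples from participants in the third trimester". Secondary outcomes says what it stands for: "Gas chromatography mass spectrometry measurement of metformin in maternal plasma to determine adherence".

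The comparator is placebo. Under Randomisation: "Eligible participants will be randomly assigned to active treatment with metformin or an identical looking placebo". Exposure can vary between women for reasons that arise after randomisation. Under Dose changes, "The local investigator or participant may alter the treatment regimen at his/her discretion", up to a stated maximum, and the Intervention section ties escalation to what the woman can tolerate.

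Type of analysis and statistical tests fixes the main analysis set: "The primary analysis will be by intention to treat". That section names neither a comparator nor a method for the restricted analysis.

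**The concern.** A drug level in the third trimester is a consequence of allocation, tolerance and adherence. Placebo women essentially cannot have one. Three problems follow.

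- **Restricting both arms** removes the comparator. The only placebo women left would be any who received metformin outside the trial. The Background notes that the drug is endorsed "as a treatment for gestational diabetes", so such a woman could enter the set because of a complication.
- **Restricting only the metformin arm** sets women who tolerated and took the drug against placebo women of every kind. There is no placebo drug level by which to pick their counterparts.
- **Needing a third-trimester sample** further conditions on still being pregnant and attending.

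The Background also reports that birth weight is related to maternal pre-pregnancy weight and to weight gain. If tolerance or adherence is related to either, which is an assumption, the selected women differ in prognosis whatever the drug does.

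What is at stake is interpretation. A non-randomised estimate labelled efficacy could be reported beside a randomised intention-to-treat result and be preferred to it, especially if the latter were null. The Primary objective already uses the word efficacy for the randomised comparison, so the label does not keep the two apart.

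**Working it through.** **1. The plan's own figures.** The sample size section gives a difference of 0.2 kg and an SD of 0.6 kg, so 0.2/0.6 = 0.333 SD, two-sided 5%. A two-sample t calculation gives 142.2, rounded up to 143 per group, for 80% power and 162.6, rounded up to 163, for 85%. Both stated sizes reproduce and are not in dispute. The plan attaches no figure to the restricted analysis.

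**2. Bias when the placebo arm is kept whole.** Let c be the share of metformin women with a pharmacological level. Let δ be the difference in mean birthweight z-score, regardless of drug, between women who would and would not reach it. Suppose the drug has no effect.

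- Mean in selected metformin women: m_A
- Mean in all placebo women: c·m_A + (1 − c)·m_N
- Difference: (1 − c)(m_A − m_N) = (1 − c) × δ

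**3. Numbers.** Neither c nor δ is in the document, so both are assumed over a range. The false-positive rate is two-sided and uses a normal approximation with unit SD, 163 randomised per arm and SE = √(1/(163c) + 1/163). Each cell shows bias in SD and, in brackets, the false-positive rate.

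| c | δ = 0.1 | δ = 0.2 | δ = 0.3 | δ = 0.5 |
|---|---|---|---|---|
| 0.5 | 0.05 (6.6%) | 0.10 (11.4%) | 0.15 (19.8%) | 0.25 (45.3%) |
| 0.65 | 0.035 (5.9%) | 0.07 (8.7%) | 0.105 (13.4%) | 0.175 (28.9%) |
| 0.8 | 0.02 (5.3%) | 0.04 (6.3%) | 0.06 (8.0%) | 0.10 (13.6%) |
| 0.9 | 0.01 (5.1%) | 0.02 (5.4%) | 0.03 (5.8%) | 0.05 (7.2%) |

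Against the 0.33 SD target the extremes are 0.01/0.33 = 3% and 0.25/0.33 = 76%. A middle case, c = 0.65 and δ = 0.3, gives 0.35 × 0.3 = 0.105 SD, or 32% of target. At δ = 0 the bias is zero for every c. A negative δ gives the same sizes with the opposite sign.

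**4. The randomised alternative.** If metformin use on placebo is negligible, the complier average causal effect is the intention-to-treat difference divided by c, and its standard error is about 1/c times as large: ×1.11 at c = 0.9, ×1.25 at 0.8, ×1.54 at 0.65 and ×2.0 at 0.5.

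At 163 per arm the intention-to-treat standard error is √(2/163) = 0.111 SD. At c = 0.65 the complier estimate has 0.111/0.65 = 0.170 SD, and the restricted comparison has √(1/106 + 1/163) = 0.125 SD. The restricted analysis therefore looks more precise, but that precision comes at the cost of the randomised comparison.

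**The case against.** **It is only a secondary objective.** This stands. The primary analysis, the sample size and the main conclusion do not depend on it. The wording also tells the reader that a different, on-drug question is being asked.

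**The article names no comparator, and an unseen analysis plan may supply one.** This stands in part. Placebo women could be restricted by treatment diary or tablet count, which would avoid the exact contrast computed above. It would not restore randomisation: those who keep taking placebo are not the counterparts of those who tolerate metformin and reach a given level. An analysis plan that used a complier estimate would replace the stated restriction, so the objective would still need rewording.

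**Bias is possible, not shown.** This stands. A reader might infer that the estimate is biased, or biased in favour of metformin. The document gives neither the adherent share nor any link between adherence and birthweight z-score, so neither the size nor the sign can be derived. A narrower range could be chosen to make the bias look more definite, but nothing in the document supports one.

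**The side arguments have limits.** A reader might infer that placebo women will receive metformin for gestational diabetes. The article says only that this use is endorsed. Loss before sampling may also be modest: the visit table schedules stored blood at 28 and 36 weeks, so if the earlier sample is used, mainly losses and births before about 28 weeks go unsampled.

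**The complier estimate has weaknesses of its own.** A woman who took metformin for months and stopped before sampling would count as unexposed, which strains the exclusion restriction. Tablet counts in the placebo arm measure placebo tablets and must not be read as exposure. Both are dealt with under the fix.

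**Conclusion.** The point holds as a weakness of a secondary objective that should be corrected. The stated restriction selects on a post-randomisation status that essentially only one arm can have, so its result is not a randomised comparison and is open to selection bias of unknown sign.

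With placebo kept whole, the bias lies between 0.01 and 0.25 SD over the assumed ranges and vanishes if adherence is unrelated to prognosis. So wide a range means that the size is essentially undetermined. The formula does not describe a comparison in which placebo women are also selected by diary or tablet count.

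A reader might infer that the trial's main conclusion is compromised. The document does not support that, because the primary analysis is by intention to treat.

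**What to change.** Reword the objective to estimate the complier average causal effect of metformin on the birthweight z-score, and specify the following.

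- **Population:** all randomised women with a recorded birth weight.
- **Method:** two-stage least squares with randomised allocation as the instrument, adjusted for treatment centre and BMI stratum.
- **Exposure:** metformin actually received, defined as detectable metformin in the third-trimester sample. For metformin-arm women without a sample, use diary and tablet count. Placebo-arm women count as unexposed unless metformin is detected or off-trial metformin is recorded. Placebo tablet counts never count as exposure.
- **Sensitivity analysis:** also count as exposed those metformin-arm women who took the drug earlier but had stopped by sampling.
- **Reporting:** label any comparison restricted by drug level descriptive.

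Detectable rather than pharmacological metformin is a deliberate change of exposure. Women below a pharmacological cut-off may still respond, which would breach the exclusion restriction.

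The cost is one reworded objective and a small extra analysis. The assay, diary and tablet counts are already planned, although the assay must be run on samples from both arms and off-trial metformin must be recorded. The estimate has a standard error about 1/c times that of intention to treat, and it rests on the stated assumption that allocation affects birth weight only through metformin received.
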